| dsDNA positive ever, no. (%)                           |                                          |                                              |                                               |                                           |                                           |
| SLEDAI 2K, score 0-105                                 |                                          |                                              |                                               |                                           |                                           |
| SLEDAI 2K, without PD, score 0-103                     |                                          |                                              |                                               |                                           |                                           |
| SLICC DI, score 0- 48                                  |                                          |                                              |                                               |                                           |                                           |
| SLICC DI, without PD, score 0-43                       |                                          |                                              |                                               |                                           |                                           |
| Dry cough, composite                                   |                                          |                                              |                                               |                                           |                                           |
| Dry cough, status:                              |                                          |                                              |                                               |                                           |                                           |
| Never, no. (%)                                         |                                          |                                              |                                               |                                           |                                           |
| Prior, no. (%)                                         |                                          |                                              |                                               |                                           |                                           |
| Present, no. (%)                                       |                                          |                                              |                                               |                                           |                                           |
| Tightness in chest, composite, no. (%)                 |                                          |                                              |                                               |                                           |                                           |
| Tightness in chest, status:                     |                                          |                                              |                                               |                                           |                                           |
| Never, no. (%)                                         |                                          |                                              |                                               |                                           |                                           |
| Prior, no. (%)                                         |                                          |                                              |                                               |                                           |                                           |
| Present, no. (%)                                       |                                          |                                              |                                               |                                           |                                           |

Planned univariate analysis. PD – Pulmonary Disease according to multidisciplinary discussion; 95% CI – 95% Confidence Interval; Airway – Airway Disease according to multidisciplinary discussion; Pleural – Pleural Disease according to multidisciplinary discussion; ILD – Interstitial Lung Disease positive according to multidisciplinary discussion; SLS – Shrinking

Lung Syndrome according to multidisciplinary discussion; CTD – Connective Tissue Disease; APL– Antiphospholipid Antibodies; dsDNA – anti-double stranded DNA antibodies; SLEDAI 2K – Systemic Lupus Erythematosus Disease Activity Index 2000; SLICC DI – Systemic Lupus International Collaborating Clinics /American College of Rheumatology Damage Index for Systemic Lupus Erythematosus. The reported Odds Ratio and 95% confidence interval is between participants positive and negative in regards of PD / Airway / Pleural / ILD / SLS.

| Pulmonary function test measures. | N | Airway disease present | N | Airway disease absent | Contrast between groups (95%CI) |
|------------------------------------------|----------|-------------------------------|----------|------------------------------|----------------------------------------|
| Body plethysmography:             |          |                               |          |                              |                                        |
| FEV 1 , %*                    |          |                               |          |                              |                                        |
| FEV 1 low**, no. (%)          |          |                               |          |                              |                                        |
| FVC, %*                                  |          |                               |          |                              |                                        |
| FVC low**, no. (%)                       |          |                               |          |                              |                                        |
| FEV 1 /FVC (ratio)            |          |                               |          |                              |                                        |
| FEV 1 /FVC below 70%, no. (%) |          |                               |          |                              |                                        |
| TLC, %*                                  |          |                               |          |                              |                                        |
| TLC low**, no. (%)                       |          |                               |          |                              |                                        |
| Diffusion test:                   |          |                               |          |                              |                                        |
| DLCO, %*                                 |          |                               |          |                              |                                        |
| DLCO low**, no. (%)                      |          |                               |          |                              |                                        |
| KCO, %*                                  |          |                               |          |                              |                                        |
| KCO low**, no. (%)                       |          |                               |          |                              |                                        |
| 6 min walk test:                  |          |                               |          |                              |                                        |
| Distance, %*                             |          |                               |          |                              |                                        |
| Distance low**, no. %                    |          |                               |          |                              |                                        |
| Desaturation, (Saturation delta)         |          |                               |          |                              |                                        |
| Desaturation below 93% #, no. %          |          |                               |          |                              |                                        |

Value will be means and SDs unless otherwise indicated. \*- % of expected; \*\* - low is defined as below 80% of expected; # - If COPD or emphysema 88%; Airway disease positive – Airway Disease according to multidisciplinary discussion; FEV1 – Forced Expiratory Volume in One Second; FVC – Forced Vital Capacity; TLC – Total Lung Capacity; DLCO - Diffusing capacity of the Lung for Carbon Monoxide; KCO – Carbon Monoxide Transfer Coefficient. Contrasts for continuous measures will be based on the difference between means with 95% CIs, while dichotomous outcomes will be based on risk differences with 95% CIs.

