## METHODS

The present study is part of a larger research initiative. Findings on the associations between PD and PD subtypes and pulmonary function test (PFT) measures, thoracic ultrasound, diaphragmatic ultrasound, and additional biomarkers will be reported in separate publications. A separate study will examine PD diagnoses and selected outcomes, including thoracic and diaphragmatic ultrasound, in newly diagnosed systemic lupus erythematosus (SLE) patients. Patients were identified through a systematic search of hospital records across all institutions in the Southern Denmark Region. The search includes visits between July 1, 2021, and June 30, 2023, coded as related to SLE or SLE-associated diseases. Participants were enrolled between August 1, 2023, and October 31, 2024. Statistical analyses will commence upon finalization and approval of this SAP.

At a single visit day all tests were performed. All participants start with an outpatient visit, where the primary investigator review the participants' medical history, note the patients' disease activity and damage. Hereafter the participants undergo pulmonary function testing, HRCT scan, and blood and urine samples. Questionnaires are filled out before the visit. The HRCT scans are described after the visits, and finally the participants are diagnosed, at a multidisciplinary discussion (MDD). The study will be reported in accordance with the STROBE guideline (Strengthening of Reporting Observational Studies in Epidemiology). It is not always possible to measure a precise saturation in a six-minute walk test, why we have scored them as good, medium, poor, too bad to use. Good is tests without any outages. Medium is tests with outages, that which we do not suspect affect the measurement. Poor is tests where we suspect, that the outages affect the results. We will only use tests that score good or medium, and the rests will be regarded as missing values.

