## **Logistical regression: Searching for risk factors that are associated with presence of different forms of PD**

Mock-up Table 4. We aim to explore whether one or more clinical measures collected at baseline are associated with the presence of PD. The dependent variable will be the presence or absence of a PD condition of interest (i.e.,  $Y=1$  if yes, otherwise  $Y=0$ ). Logistic regression is the best approach for identifying predictors when the outcome variable is binary (i.e., presence vs. absence of PD) and the goal is to estimate the association between predictor variables and the probability of the outcome while enabling adjustments for potential confounders. Independent variables, as listed in Table 4 and appendix 3, will be analysed in univariate logistic regression to identify potential associations with clinically significant PD conditions. Odds ratios (ORs) with 95% CIs will be used to quantify the strength of associations, with 95% CIs excluding 1 considered indicative of potential significance. In multiple logistic regression analyses we plan to investigate associations that were significant by univariate analyses, however, only a subset of independent variables will be expected to remain statistically significant and independently associated with PD conditions.

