| Desaturation, (Saturation delta)         |     |            |           |                                 |
| Desaturation below 93% #, no. %          |     |            |           |                                 |

Value will be means and SDs unless otherwise indicated. \* - % of expected; \*\* - low is defined as below 80% of expected; # - If COPD or emphysema 88%. SLE – Systemic Lupus Erythematosus; PROMs – Patient Reported Outcome Measures; PFT – Pulmonary Function Tests; PD – Pulmonary Disease according to multidisciplinary discussion; APL– Antiphospholipid Antibodies; dsDNA – anti-double stranded DNA antibodies; SLEDAI 2K – Systemic Lupus Erythematosus Disease Activity Index 2000 (16); PGA – Physician Global Assessment (17); LLDAS – Lupus Low Disease Activity State (18); DORIS – Definition of

Remission in SLE (19); SLICC DI – Systemic Lupus International Collaborating Clinics /American College of Rheumatology Damage Index for Systemic Lupus Erythematosus (20); LIT – questionnaire inspired by “Lupus Impact Tracker” (21); SLAQ – Systemic Lupus Activity Questionnaire (22); MRC – Medical Research Council Dyspnoea Scale; FEV1 – Forced Expiratory Volume in One Second; FVC – Forced Vital Capacity; TLC – Total Lung Capacity; DLCO - Diffusing capacity of the Lung for Carbon Monoxide; KCO – Carbon Monoxide Transfer Coefficient.

We plan to present the prevalence of subgroups of PD in a table, see table 3.

**Table 3.** Diagnoses of pulmonary diseases among Systemic Lupus Erythematosus patients.

| Groups of PD | Subgroups of PD                 | Prevalence, no. (%) |
|--------------|---------------------------------|---------------------|
| Airway       |                                 |                     |
|              | Asthma                          |                     |
|              | Bronchiectasis                  |                     |
|              | Obliterative Bronchiolitis      |                     |
|              | Infectious Bronchiolitis        |                     |
|              | COPD                            |                     |
|              | Emphysema                       |                     |
|              | Other                           |                     |
| Pleural      |                                 |                     |
|              | Pleuritis                       |                     |
|              | Pleural disease of diaphragm    |                     |

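### The binary desaturation row uses a lower cut-off for COPD and emphysema, which pulls its PD and airway-disease contrasts downwards by construction

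*SAP*

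**What the plan says.** The SAP dichotomises saturation in the six-minute walk test in the row "Desaturation below 93% #, no". The hash footnote lowers the threshold for one set of participants: "If COPD or emphysema 88" (per cent). Row and footnote appear in Table 2, Appendices 1a-1d and Appendix 3.

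Table 3 lists COPD and emphysema as subgroups of the Airway group, which is itself a group of PD. The groups compared are set by the multidisciplinary discussion. In Appendix 1a the label is "Airway disease positive – Airway Disease according to multidisciplinary discussion". The Methods section places that discussion after the tests: "finally the participants are diagnosed, at a multidisciplinary discussion (MDD").

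The row is used in two ways. In Table 2 and Appendices 1a-1d it is contrasted between disease-present and disease-absent participants. The appendices state that "dichotomous outcomes will be based on risk differences with 95% CIs". Table 2 has a contrast column with a 95% CI but does not name the measure. In Appendix 3 the row is an independent variable in univariate logistic regressions for PD, airway disease, pleural disease, ILD and SLS. For these, the logistic regression section says "The dependent variable will be the presence or absence of a PD condition of interest".

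The SAP gives no reason for the split threshold and no analysis with a single one. Its section on deviations does not change the rule.

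**The concern.** A between-group contrast is interpretable only if the characteristic is measured in the same way in both groups. Here the coding of the characteristic depends on diagnoses that help to define the groups. A participant with COPD whose saturation falls to 90% is not counted, while a participant without lung disease at 90% is.

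For airway disease and PD the two thresholds are therefore not spread evenly over the groups. Part of the observed contrast would reflect the coding and not saturation. The logistic regression section carries significant univariate associations into multiple regression. A distorted odds ratio could thus bring the variable into that model, or a true association could be missed.

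The other dichotomised function tests use one threshold for everyone (below 80% of expected, or FEV1/FVC below 70%). Only this row changes with diagnosis.

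**Working it through.** The SAP states no expected rate or distribution for this row, so there is no planned figure to reproduce.

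**Inputs from the SAP:** cut-offs of 93% and 88%; COPD and emphysema inside Airway and PD (Table 3); risk difference (Appendices 1a-1d); odds ratio (Appendix 3).

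**Assumptions:** the COPD/emphysema label is the diagnosis from the multidisciplinary discussion. Lowest saturation S is normal with SD 3 (2.5 to 4 also tried) and mean 95 without airway disease. Let f be the COPD/emphysema share of the airway group. Write C for COPD/emphysema, O for other airway disease and N for no airway disease.

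**Formulas**

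- Planned RD = f·P(S<88|C) + (1-f)·P(S<93|O) - P(S<93|N)
- RD with 93% for all = f·P(S<93|C) + (1-f)·P(S<93|O) - P(S<93|N)
- Planned minus common = -f·P(88≤S<93|C), which cannot be positive

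The 93% comparator only shows the effect of the split. It is not a proposal for that value.

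**Identical saturation in all groups (true contrast zero)**

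P(S<93) = Φ((93-95)/3) = 0.2525 and P(S<88) = Φ((88-95)/3) = 0.0098. The difference is 0.2427.

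- Airway: RD = -f × 0.2427, which is -6.1, -12.1, -18.2 and -24.3 points for f = 25%, 50%, 75% and 100%. The odds ratios are 0.70, 0.45, 0.22 and 0.03. For f = 50%, the planned proportion is 0.2525 - 0.1213 = 0.1312. Its odds of 0.151 against 0.338 give 0.45.
- PD: with COPD/emphysema as 10%, 20% or 40% of the PD group, RD = -2.4, -4.9 or -9.7 points.

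**Airway contrast when saturation truly differs (SD 3, N mean 95)**

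| Mean C | Mean O | f | RD, 93% for all | Planned RD |
|---|---|---|---|---|
| 93 | 95 | 50% | +12.4 | -10.2 |
| 92 | 94 | 25% | +18.2 | +4.7 |
| 92 | 94 | 50% | +24.8 | -2.2 |
| 91 | 94 | 50% | +30.6 | +1.2 |
| 91 | 94 | 75% | +40.0 | -4.1 |
| 90 | 94 | 50% | +35.3 | +5.8 |
| 89 | 94 | 50% | +38.7 | +11.7 |

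First row: with 93% for all, 0.5×0.500 + 0.5×0.2525 = 0.376. Under the plan, 0.5×0.048 + 0.5×0.2525 = 0.150. Both are set against 0.2525. The odds ratio moves from 1.79 to 0.52.

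With C only 1 to 2 points below N, and O equal to N, the sign reversed at every f from 25% to 100% and every SD tried. With a C mean of 88 to 90 it did not reverse; the contrast shrank (to zero at mean 90 and f = 100%).

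**ILD contrast, identical saturation**

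RD = -(share in present group - share in absent group) × 0.2427. Shares of 5% and 20% give +3.6 points, 20% and 5% give -3.6, and equal shares give 0. The same formula applies to pleural disease and SLS.

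**The case against.** Several points on the other side have weight.

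- **Source of the label.** The footnote does not say whether COPD or emphysema comes from the multidisciplinary discussion, the medical history or the scan. Appendix 2 lists emphysema as an HRCT finding outside its Airways group. A reader might infer that every PD-absent participant is judged at 93%. The SAP does not establish that: a scan-based or history-based label could give some disease-absent participants the 88% cut-off. This stands, and the gap itself needs closing.
- **Sign reversal.** A reader might infer that the contrasts will point the wrong way. The SAP has no saturation data and no COPD/emphysema shares, and reversal appears only for some assumed values. This stands. What holds without those values, given the label from the multidisciplinary discussion, is the direction of the shift relative to 93% for all.
- **ILD and pleural disease.** A reader might infer that the bias runs the opposite way there, because most COPD patients fall in the absent group. What matters is the share within each group, which the SAP does not give, so no direction can be claimed.
- **Importance.** The primary objective is PD prevalence. The regressions are exploratory, the intervals are not meant to replace hypothesis tests, and the rule is disclosed in each footnote. The continuous saturation delta stands beside the row in every affected table. The deviations section later moves Table 2 out of the main text and drops SLS. These points lower the severity.
- **Clinical rationale.** A diagnosis-specific threshold may be deliberate and explained in a protocol not shown. That could justify a descriptive count, but it would not make the two groups comparable on this row.

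**Conclusion.** The concern holds for the PD and airway-disease contrasts (Table 2, Appendix 1a) and the corresponding odds ratios in Appendix 3, provided that the label is the diagnosis from the multidisciplinary discussion. The downward pull then follows from the coding. Its size depends on assumptions. With equal saturation (mean 95, SD 3) it is about 6 to 24 points for airway disease at shares of 25% to 100%, and about 2 to 10 points for PD at shares of 10% to 40%. A true positive contrast is attenuated. It may be reversed when the saturation deficit is moderate or COPD/emphysema makes up much of the group.

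For ILD, pleural disease and SLS, distortion arises only if the COPD/emphysema share differs between the groups, and its direction is unknown. This should be fixed but does not threaten the study's main result: the prevalence estimate and the continuous delta are unaffected.

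**What to change.** In every between-group contrast and regression (Table 2, Appendices 1a-1d, Appendix 3), apply one common cut-off to all participants. The choice of value belongs to the investigators. Alternatively, drop the binary row from those comparisons and rely on the saturation delta already listed. Keep the diagnosis-specific count only as description. State in the footnote how COPD and emphysema are ascertained: multidisciplinary discussion, history or HRCT.

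The cost is a revised footnote and one recoded variable, with the affected rows rerun. No new data are needed. If results already exist, the change should be recorded in the section on deviations.

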**Appendix 1b. Pulmonary function tests according to the prevalence of pleural disease.**

| Pulmonary function test measures. | N | Pleural disease present | N | Pleural disease absent | Contrast between groups (95%CI) |
|------------------------------------------|----------|--------------------------------|----------|-------------------------------|----------------------------------------|
| Body plethysmography:             |          |                                |          |                               |                                        |
| FEV 1 , %*                    |          |                                |          |                               |                                        |
| FEV 1 low**, no. (%)          |          |                                |          |                               |                                        |
| FVC, %*                                  |          |                                |          |                               |                                        |
| FVC low**, no. (%)                       |          |                                |          |                               |                                        |
| FEV 1 /FVC (ratio)            |          |                                |          |                               |                                        |
| FEV 1 /FVC below 70%, no. (%) |          |                                |          |                               |                                        |
| TLC, %*                                  |          |                                |          |                               |                                        |
| TLC low**, no. (%)                       |          |                                |          |                               |                                        |
| Diffusion test:                   |          |                                |          |                               |                                        |
| DLCO, %*                                 |          |                                |          |                               |                                        |
| DLCO low**, no. (%)                      |          |                                |          |                               |                                        |
| KCO, %*                                  |          |                                |          |                               |                                        |
| KCO low**, no. (%)                       |          |                                |          |                               |                                        |
| 6 min walk test:                  |          |                                |          |                               |                                        |
| Distance, %*                             |          |                                |          |                               |                                        |
| Distance low**, no. %                    |          |                                |          |                               |                                        |
| Desaturation, (Saturation delta)         |          |                                |          |                               |                                        |
| Desaturation below 93% #, no. %          |          |                                |          |                               |                                        |

Value will be means and SDs unless otherwise indicated. \* - % of expected; \*\* - low is defined as below 80% of expected; # - If COPD or emphysema 88%; Pleural disease present – Pleural Disease according to multidisciplinary discussion; FEV1 – Forced Expiratory Volume in One Second; FVC – Forced Vital Capacity; TLC – Total Lung Capacity; DLCO - Diffusing capacity of the Lung for Carbon Monoxide; KCO – Carbon Monoxide Transfer Coefficient. Contrasts for continuous measures will be based on the difference between means with 95% CIs, while dichotomous outcomes will be based on risk differences with 95% CIs.

